#### Measurement of cost and outcomes (objectives 3 and 4)

There is a lack of robust evidence around the cost-effectiveness of alternative feeds for gastrostomy fed children. To address this, we will describe the costs and outcomes for those children with a formula diet and with a home-blended diet (addressing objectives 3 and 4). The formula feed group will act as the treatment as usual.

### Generating cost estimates

Unit costs for healthcare interactions will be collected from published sources (eg, PSSRU Unit Costs of Health and Social Care) and applied to the relevant resource use. The costs of healthcare interactions will be calculated by the product of unit cost and resource use analyses.

The cost of non-healthcare interactions, including the cost of the blended diet constituents and time taken to prepare, will be estimated separately using published estimates where feasible. Sensitivity analyses will be conducted where alternative assumptions would generate substantially different cost estimates (eg, if there are substantial differences between parental report and HES data).

### Generating estimates of outcomes

We will describe and summarise estimates of parent changes in health-related quality of life (EQ-5D-5L) and child (either PedsQL or QoL questionnaire^22^). We will describe these for both groups within the cohort.

We will report total costs, mortality and adverse event rates associated with both home-blended and formula feeds in a cost-consequences framework.

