**Methods and analyses:**

This is a mixed methods study of children (aged 6 months to 18 years) who are gastrostomy feed dependent recruited via general, community and specialist paediatric and dietetic services.

*Workstream*
*1* (*WS1*): a qualitative study involving semistructured interviews with parents (n~20) and young people (n~5–10), and focus groups with health professionals (n~25), will provide evidence of appropriate outcome measures and the feasibility/acceptability of proposed data collection methods for WS2. It will gather data on: desired outcomes of gastrostomy feeding, variability in diets and reasons; use of oral feeding; perceived benefits of the alternative diets, resources associated with gastrostomy feeding and safety issues. Data will be analysed using thematic analysis.

*WS2*: a cohort study of 300 children who are gastrostomy fed. Data will be collected at months 0, 9 and 18 from parents, children (if appropriate) and clinicians using standardised measures and questionnaires developed specifically for the study. Data collected will include gastrointestinal symptoms, health and other outcomes (child, parent), dietary intake, anthropometry, healthcare usage, safety outcomes and resource use. Outcomes in the home-blended and formula groups will be compared using appropriate multiple regression analyses.

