**Study registration number:**

ISRCTN13977361.

Strengths and limitations of this studyA multicentre study of a large number of children who are gastrostomy fed.Key outcomes will be determined from qualitative work with parents, young people and professionals.The study will use validated measures for gastrointestinal symptoms, nutritional intake, health and other outcomes, and quality of life data collection.This is an observational study with no randomisation, therefore confounding and bias may be of concern.

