## Methods and analyses

The research question is: What are the risks, benefits and resource implications for using home-blended food for children with gastrostomy tubes compared with currently recommended formula feeds?

The objectives are:

To identify the important outcomes of gastrostomy feeding for parents, young people and health professionals.To assess the safety of home-blended diets for children who are gastrostomy fed compared with liquid formula diets.To identify and quantify the benefits of home-blended diets compared with liquid formula feeds for children who are gastrostomy fed and their parents.To identify and quantify the resources (family and statutory services) required to support home-blended diets compared with formula feeds.To assess whether long-term follow-up of children who are gastrostomy fed is feasible using routine data sources.

This study will use a mixed methods exploratory sequential design^10^ with two workstreams (WS), with findings from WS1 informing the design and methods for WS2. The research team comprises clinical and methodological experts including applied social scientists (leading WS1) and a clinical epidemiologist leading WS2.

### Workstream 1

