#### Data collection

Data will be collected at three time points: at baseline and then at 9 and 18 months. At each time point, data on a range of outcomes as well as relevant clinical and feeding information will be collected from parents/children/young people and clinicians. See table 2 for summary of proposed outcomes and data sources (these are subject to change following WS1).

**Table 2 T2:** Proposed variables and data sources for WS2

Variable	Type of variable	Proposed measure	Source	Timings of data collection (months)		
				0	9	18
Participant characteristics/predictors						
Age	Predictor	Date of birth	Parent	√		
Ethnicity		Census groups	Parent	√		
Deprivation		Index of Multiple Deprivation (based on postcode)	Parent	√	√	√
Parental educational attainment		Census groups	Parent	√		
Household composition		Number of children, marital/living status	Parent	√	√	√
Diagnosis			Paediatrician	√		
Comorbidities			Paediatrician	√	√	√
All medications			Paediatrician	√	√	√
Complexity		Disability Complexity Scale^23 24^	Paediatrician	√	√	√
Length of time gastrostomy fed at T0		Months/years	Parent	√		
Comparator						
Diet: formula/blended	Main grouping variable		Parent	√	√	√
Outcomes						
Nutritional content of feeds	Outcome	Commercial for formula	Dietitian/parent	√	√	√
		myfood24^15^	Parent	√	√	√
Anthropometric data	Outcome	Height or length Weight Triceps skinfold thickness or mid-arm circumference	Dietician Paediatrician	√	√	√
Gastrointestinal symptoms	Outcome	PedsQL gastrointestinal^19^	Parent/child	√	√	√
Child quality of life	Outcome	PedsQL generic module^18^	Parent/child	√	√	√
Parental quality of life	Outcome	EQ-5D-5L^25^ Parenting Morale Index^26^	Parent	√	√	√
Healthcare use	Outcome	Client service receipt inventory^27^	Parent	√	√	√
	Outcome	Number of hospital admissions Number of accident and emergency (A&E) attendances	HES data	√	√	√
Safety	Outcome	Tube blockages Number of stoma infections Number of gastrointestinal infections	Parent			
	Outcome	Number of hospital admissions and A&E attendance associated with child’s gastrostomy/diet	HES and parent	√	√	√
Family resource use	Outcome	Time preparing feeds; impact on other caring/parenting Financial costs	Parent	√	√	√
Non-staff NHS resource use	Outcome	Cost of formula and packaging Dietetic resources	Dietitian	√	√	√

EQ-5D-5L, 5-level version of EuroQol-5 Dimension; HES, Hospital Episodes Statistics; NHS, National Health Service; PedsQL, Pediatric Quality of Life Inventory; WS2, workstream 2.

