#### Assessing safety (objective 2) and benefits (objective 3)

The safety and benefits of blended diet compared with formula diet will be assessed using multivariable regression analyses. The type of regression will depend on the outcome of interest: logistic (tube blockage, appropriate nutritional content; yes/no), linear (PedsQL gastrointestinal module score, BMI SDS or upper arm circumference, calories, Parenting Moral Index (PMI), EQ-5D), Poisson or negative binomial (number of A&E or hospital admissions for infections or complications of gastrostomy tube). Each analysis will account for the multiple confounding factors in this population (age, underlying diagnoses, comorbidities, outpatient attendance, parental factors, socioeconomic status) and the main covariate of interest will be feeding status (blended vs formula). Study site will be added as a random effect to the models to allow for site-level variation. Estimates and 95% CIs will be reported from the regression model for each outcome measure.

The flow of participants through the study will be detailed including the number of individuals contributing to each analysis. The amount of missing data will be summarised for each outcome measure and multiple imputation will be used to assess the robustness of the results. Results will be compared with the complete case analyses and important differences discussed. Sensitivity analyses will be considered to explore departures from the missing at random assumption.

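### As stated, total costs and most resource use are only described by diet group, although objective 4 asks for a comparison with formula and the groups are not randomised

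*Protocol article*

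**What the plan says.** The objectives in the protocol article (Methods and analyses) include one on benefits, "To identify and quantify the benefits of home-blended diets compared with liquid formula feeds for children who are gastrostomy fed and their parents", and one on resources, "To identify and quantify the resources (family and statutory services) required to support home-blended diets compared with formula feeds". Both are comparative.

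The abstract lists resource use among the data to be collected and then states: "Outcomes in the home-blended and formula groups will be compared using appropriate multiple regression analyses". The strengths and limitations list adds: "This is an observational study with no randomisation, therefore confounding and bias may be of concern".

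The section Assessing safety (objective 2) and benefits (objective 3) sets out multivariable regressions adjusted for age, diagnoses, comorbidities, outpatient attendance, parental factors and socioeconomic status, with site as a random effect. It assigns outcomes to model types. The linear entry reads "linear (PedsQL gastrointestinal module score, BMI SDS or upper arm circumference, calories, Parenting Moral Index (PMI), EQ-5D". The count models cover A&E visits and admissions for infections or tube complications. Estimates with 95% CIs are promised for each outcome measure.

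Objective 4 is taken up under Measurement of cost and outcomes (objectives 3 and 4), where "we will describe the costs and outcomes for those children with a formula diet and with a home-blended diet". Generating cost estimates deals with unit costs and with sensitivity to costing assumptions. Generating estimates of outcomes says that parent and child quality of life will be described for both groups, and ends: "We will report total costs, mortality and adverse event rates associated with both home-blended and formula feeds in a cost-consequences framework".

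**The concern.** The article recognises that the diet groups may differ in ways that confound comparisons, and it plans adjustment for safety and benefits. For costs it commits only to description by group, in the one place where objective 4 is analysed. Diagnosis, comorbidity and deprivation plausibly affect both what a child's care costs and which diet the family uses. An unadjusted cost difference could therefore have the wrong size or the wrong sign. Formula feeding is named as treatment as usual and the section opens with the lack of robust cost-effectiveness evidence, so readers will treat the two columns of a cost-consequences table as a comparison.

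A smaller matter of clarity concerns child quality of life. Table 2 gives the "PedsQL generic module" as the child quality-of-life outcome, but it is absent from the list of linear outcomes, and the economic section only describes it.

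**Working it through.** **1. Which outcomes have a named adjusted model?** The cost point turns on the text, because the article states no cost figure that could be reproduced.

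| Item | Status in the article | Named in an adjusted model | Described or reported by group |
|---|---|---|---|
| Total NHS and family costs | Built from Table 2 resource items | No | Yes |
| All-cause admissions and A&E visits; service receipt inventory | Table 2 outcome | No | Through costs |
| Formula and packaging cost, dietetic resources | Table 2 outcome | No | Through costs |
| Family preparation time and money | Table 2 outcome | No | Through costs |
| Gastrostomy-related admissions and A&E visits | Table 2 outcome | Yes (Poisson or negative binomial) | Presumably, among adverse events |
| EQ-5D | Table 2 outcome | Yes (linear) | Yes |
| PedsQL generic | Table 2 outcome | Not by name; general sentences apply | Yes |
| Mortality | Death certificate linkage | No | Yes |

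The first four rows make up most of objective 4. The regression section is headed objectives 2 and 3 and opens with safety and benefits, so these rows fall outside its stated scope.

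**2. What an unadjusted cost contrast could do (all inputs assumed).** Let high-complexity children cost 3 units and others 1, with no effect of diet. If 60% of formula and 40% of blended children are high-complexity:

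- formula mean = 0.6 × 3 + 0.4 × 1 = 2.2
- blended mean = 0.4 × 3 + 0.6 × 1 = 1.8
- crude ratio, blended to formula = 1.8 / 2.2 = 0.82, an apparent 18% saving

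With the same imbalance reversed, the ratio is 2.2 / 1.8 = 1.22, an apparent 22% excess. With no imbalance it is 1. The article gives neither the direction nor the size of the true imbalance.

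**3. Child quality of life, if only an unadjusted contrast were reported.** The Sample size section gives 300 children at two to one, hence 200 and 100, and SD 20. Taking a 95% level (assumed, as none is stated), its precision for proportions reproduces: 1.96 × √(0.25/100) = 9.8%, within the stated 10%. For a score, SD/√n = 20/√100 = 2.0 and 1.96 × 2.0 = 3.92. The stated 4 points thus matches a 95% half-width and not an SE, which is a separate matter.

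- SE of a group difference = 20 × √(1/100 + 1/200) = 2.45
- bias = complexity gap in SD units × correlation with the score × SD
- assumed gap 0.3, correlation 0.3: 0.3 × 0.3 × 20 = 1.8 points, or 1.8/2.45 = 0.73 SE
- assumed gap 0.5, correlation 0.3: 0.5 × 0.3 × 20 = 3.0 points, or 3.0/2.45 = 1.22 SE

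This applies only if the descriptive rule governs the generic score.

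**The case against.** A reader might infer that the whole of objective 4, and the child quality-of-life benefit, rest on crude contrasts. The article does not support that.

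- **Child quality of life.** The Data analyses section says outcome measures are scored ahead of statistical modelling, and the generic PedsQL is the first measure in that scoring list. The regression section promises adjusted estimates for each outcome measure, and the abstract says the same in general terms. EQ-5D is both described in the economic section and named in a linear model, so description there does not exclude adjustment elsewhere. What remains is an omission from a list.
- **Objective 4.** Gastrostomy-related admissions and A&E visits, which are part of statutory resource use, are adjusted. Formula cost, ingredients and preparation time follow largely from the diet itself, so confounding by complexity bears less on them. This weakens the point for those items, but not for all-cause healthcare use or total cost.
- **Mortality.** The article gives no death rate, and in 300 children over 18 months deaths may be too few to adjust. Reporting them descriptively is reasonable.
- **Adverse events.** It is no fault in itself that they appear both in the models and in the economic table. The article does not say which estimates will fill the table, so a contradiction cannot be presumed.
- **Analysis plan.** One is promised before analysis and may adjust costs. Model family and table layout properly belong there. But the article is not silent on costs: it states a descriptive analysis and ties it to objectives 3 and 4, against its own abstract. The EQ-5D argument does not rescue costs, because they have no counterpart in the regression section.

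**Conclusion.** The point holds for costs and most resource use. As the article states it, objective 4 asks for a comparison that the cost analysis only describes, in groups the article itself calls open to confounding. The general commitment to regression in the abstract is not carried through to the section where costs are handled. For child quality of life the point reduces to a request for clarity. For mortality there is no fault.

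The size of any bias cannot be derived from the article. The 18% cost figure and the 1.8 to 3.0 PedsQL points are illustrations on assumed inputs; they show that confounding could matter, not that it will. The conclusion also assumes that the unseen analysis plan follows the descriptive wording. If it already adjusts costs, only the article's wording needs aligning. This is an inexpensive improvement and not a threat to the study.

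**What to change.** 1. State that total NHS and family costs will be compared between diet groups with the confounder set of the safety and benefits section and a site random effect, for example by a gamma GLM with log link, or a linear model with bootstrap CIs. Outpatient attendance is in that set but is also a component of NHS cost, so in the cost models it should be a pre-baseline measure or be left out.
2. In the cost-consequences table, show adjusted differences with 95% CIs beside the crude group values, and take gastrostomy-related events from the regressions already planned.
3. Add the generic PedsQL score to the list of linear outcomes, so that the adjusted rule clearly applies to child quality of life.
4. Label mortality as descriptive.

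The cost is a few more models and some rewording. The main confounders are already collected under Table 2 and the HES linkage, so no new data are needed.

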#### Long-term follow up (objective 5)

The utility of routine data sources as an option for long-term follow-up of study participants will be assessed by examining the concordance between parent-reported data on A&E visits and hospital admissions due to infections or complications of their gastrostomy tube with HES data for the corresponding time period. Concordance will be assessed using the kappa statistic both for the total sample and separately by the home-blended and formula fed groups.

If there is concordance between the parental reported infection and gastrostomy-related healthcare usage and HES data, long-term follow-up would be possible by obtaining further extracts of HES data and ONS death certificate data. The HES data will provide future information on admissions and A&E visits due to infections and complications of the gastrostomy (blockages, revisions, replacements). The ONS data will provide date and cause(s) of death if the child has died.

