#### Sample size

Given that no data are available on the exact proportion of children who receive formula feeds versus a home-blended diet in England, various scenarios were explored to ensure that the study would be adequately powered. A sample size of 300 for the analysis (assuming there are twice as many formula fed as home blended) should enable us to estimate proportions within each group to within a margin of error of ≤10% and continuous measures (eg, Pediatric Quality of Life Inventory (PedsQL) assuming SD 20) to within an SE of 4 points.

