The PedsQL generic scale^18^ and PedsQL gastrointestinal symptoms module^19^ will be scored as per the guidelines and transformed to a score of 0–100.The height (or length) and weight will be used to calculate an age and sex-adjusted body mass index (BMI SD score (SDS)).The myfood24 data programme analyses the nutritional content of the home-blended diet and will compute the calorie intake and the macro/micronutrient content of the feed and any oral feeds. The same data for the formula fed group will have been obtained, via the dietitian, from the commercial supplier.The parent-reported number of site infections and other tube-related complications will be reported as total counts for each child.The diagnostic (International Classification of Diseases, Tenth Revision)^20^ and procedural codes (OPCS Classification of Interventions and Procedures) in the HES data will be used to identify admissions which were related to complications of the gastrostomy tubes or infections. The number of admissions and A&E attendances will be calculated for each child. Length of stay for each admission will also be calculated for the resource use analyses.Parent QoL. The EuroQol-5 Dimension (EQ-5D) visual analogue scale is scored 0–100 and the five-component scale of the 5-level version of EuroQol-5 Dimension (EQ-5D-5L) will be converted to a single score using a UK-specific value set.^21^ The 10-item Parenting Morale Index is scored from 0 to 100.

For all outcomes we will report the baseline score, follow-up scores and change score.

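### Kappa alone cannot carry the objective 5 conclusion: it hides whether HES misses events that parents report, and it falls when events are rare

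*Protocol article*

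**What the plan says.** Under *Long-term follow up (objective 5)*, the protocol article assesses routine data by "examining the concordance between parent-reported data on A&E visits and hospital admissions due to infections or complications of their gastrostomy tube with HES data". The method is a single sentence: "Concordance will be assessed using the kappa statistic both for the total sample and separately by the home-blended and formula fed groups". The conclusion is tied to the result: "If there is concordance between the parental reported infection and gastrostomy-related healthcare usage and HES data, long-term follow-up would be possible". HES would then be the future source for admissions and A&E visits, with death certificate data alongside. The section does not say whether the comparison is of counts or of any/none.

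Elsewhere the same events are counts:

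- *Data analyses*, on HES: "The number of admissions and A&E attendances will be calculated for each child".
- Table 2 (*Data collection*), safety outcome taken from HES and from parents: "Number of hospital admissions and A&E attendance associated with child’s gastrostomy/diet".
- *Assessing safety (objective 2) and benefits (objective 3)*: these events are modelled by Poisson or negative binomial regression.

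**The concern.** If HES is to stand in for parent report over ten years or more, three things need to be known: how many of the events that parents report also appear in HES, whether that proportion is similar in the two diet groups, and whether HES counts run systematically high or low. Kappa condenses agreement into one number that does not show the direction of disagreement. Its value also depends on how common the events are and, for counts, on whether it is weighted.

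Two errors are possible. HES could be accepted although it misses many parent-reported events, or it could look poor only because gastrostomy-related admissions are rare. If capture also differed by diet, later comparisons of the diets from HES would be biased, and kappa would not show in which direction.

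**Working it through.** The protocol states no kappa value, threshold or event rate, so there is no figure of its own to reproduce. From *Sample size*: 300 children with twice as many formula fed as home blended, so about 200 and 100. All accuracy and event rates below are assumptions.

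Formula: kappa = (Po − Pe)/(1 − Pe), where Po is observed agreement and Pe the agreement expected from the margins.

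**1. Direction (any/none, illustrative 300 children)**

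| | Both | Parent only | HES only | Neither | Parent-reported cases found in HES |
|---|---|---|---|---|---|
| A | 30 | 20 | 0 | 250 | 30/50 = 60% |
| B | 30 | 0 | 20 | 250 | 30/30 = 100% |

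In both, Po = 280/300 = 0.933. The margins are 50/300 and 30/300 (in one order or the other), so Pe = (1/6)(0.10) + (5/6)(0.90) = 0.767. Kappa = (0.933 − 0.767)/(1 − 0.767) = 0.71 in both. Positive agreement is also the same, 60/(60 + 20) = 0.75. The capture proportions and the HES-minus-parent difference (−20/300 against +20/300) tell A from B. The usual linear or quadratic weights are symmetric too, so weighting does not help here.

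**2. Rarity (any/none)**

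Take sensitivity 0.80 and specificity 0.95 of one source against the other, and prevalence p. The cells are 0.80p, 0.20p, 0.05(1 − p) and 0.95(1 − p). At p = 0.05, Po = 0.04 + 0.9025 = 0.9425. The second margin is 0.04 + 0.0475 = 0.0875, so Pe = 0.05 × 0.0875 + 0.95 × 0.9125 = 0.871. Kappa = 0.0713/0.1288 = 0.55.

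| Prevalence | Raw agreement | Kappa | Positive agreement |
|---|---|---|---|
| 2% | 0.947 | 0.36 | 0.38 |
| 5% | 0.943 | 0.55 | 0.58 |
| 10% | 0.935 | 0.68 | 0.71 |
| 20% | 0.920 | 0.75 | 0.80 |
| 30% | 0.905 | 0.77 | 0.83 |
| 50% | 0.875 | 0.75 | 0.86 |

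Accuracy is the same in every row. Between 5% and 20% prevalence, the gap in kappa is 0.20 here, 0.10 if specificity is 0.98 and 0.26 if it is 0.90. Between 20% and 50%, kappa moves by only about 0.02.

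**3. Size of disagreement (counts)**

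Two illustrative tables each have 20% of children discordant, split equally in both directions. The concordant children are 50% at 0 visits and 10% each at 1, 2 and 3.

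- Discordant as 0 against 1: Pe = 0.42. Unweighted kappa = (0.80 − 0.42)/0.58 = 0.66. Quadratic-weighted kappa = 1 − 0.2/2.02 = 0.90.
- Discordant as 0 against 4: Pe = 0.40. Unweighted kappa = (0.80 − 0.40)/0.60 = 0.67. Quadratic-weighted kappa = 1 − 3.2/4.0 = 0.20.

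The unweighted value does not separate the two. The mean difference is zero in both, so it does not replace weighting.

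A second check let HES counts be Poisson, with each event recalled by the parent with probability 0.8 and false reports Poisson with mean 0.05. As the mean rises from 0.3 to 3 events per child, unweighted kappa on counts falls from 0.74 to 0.44. Quadratic-weighted kappa stays at 0.81 to 0.85, but it drops to 0.69 at a mean of 0.1, so it is not immune to rarity.

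**4. Precision by group**

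Simulated 95% sampling ranges of any/none kappa, with the accuracy of step 2:

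| Prevalence | n = 100 | n = 200 |
|---|---|---|
| 5% | 0.16 to 0.85 | 0.29 to 0.76 |
| 20% | 0.56 to 0.90 | 0.62 to 0.86 |

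**The case against.** The strongest reply is that the protocol says only kappa. It does not say unweighted kappa on raw counts. Any/none kappa is a standard use, weighted kappa is also a kappa, and the choice may be fixed in the statistical analysis plan that the protocol promises before analysis. This stands. A reader might infer that the protocol has chosen the wrong measure, and the text does not support that.

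A reader might also infer that the two group kappas are bound to differ because of diet. The protocol asks whether safety differs; it gives no event rates and no expected direction. It plans no comparison of the group kappas and bases no decision on their difference. At 20% to 50% prevalence the effect is negligible, and with about 100 home-blended children a moderate effect would be lost in sampling error. The risk to the conclusion therefore lies mainly in the overall kappa.

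Some of the added measures depend on prevalence as well. With the accuracy of step 2, positive predictive value is 0.04/0.0875 = 0.46 at 5% and 0.24/0.275 = 0.87 at 30%, and positive agreement goes from 0.58 to 0.83. Parent recall is no gold standard either, and a symmetric measure has some appeal when neither source is named as the reference. Both points are fair. They argue for several measures read together, with capture reported in both directions, rather than for a single replacement.

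The protocol does foresee differences between parent report and HES under *Generating cost estimates*, but only as a trigger for sensitivity analyses of cost. That does not inform objective 5.

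The lack of direction is untouched by any of this. It holds for any/none kappa and for linear or quadratic weights, so settling the form of kappa would not cure it.

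**Conclusion.** The point holds in a limited form: kappa is acceptable but insufficient as the only stated basis for one of the five objectives. The lack of direction follows from the formula and needs no assumption about this cohort; the 60% against 100% contrast at kappa 0.71 is an illustration of it. The fall with rarity depends on event rates that the protocol does not give. It is material at roughly 2% to 10% prevalence and negligible between 20% and 50%, at the assumed sensitivity and specificity. The loss of information on counts arises only if kappa is applied to them unweighted, which the protocol neither states nor excludes. Group kappas may differ if event rates differ by diet, which remains an open question.

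**What to change.** Keep kappa, state whether it is applied to any/none or to counts, and weight it if to counts. Add the following, overall and by diet group, with 95% CIs:

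- the proportion of parent-reported cases found in HES, and the proportion of HES cases reported by parents;
- positive and negative agreement for any/none;
- the mean HES-minus-parent difference in counts per child.

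Report event rates beside each kappa. Draw the objective 5 conclusion from these measures together, without treating parent report as a gold standard.

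The cost is some wording in the analysis plan and a few more lines of analysis; no new data are needed. The drawback is wide intervals if events are rare, above all in the smaller group, but kappa has the same weakness (step 4).
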